## **8.5 Assessment of safety and reporting**

### **8.5.1 Definition of Serious Events (SEs)**

A serious event is any unfavorable event for which a causal relationship to sampling of biological material or the collection of health related personal data cannot be ruled out, and which:

- requires hospitalization or prolongation of an inpatients' hospitalization,
- results in persistent or significant disability or incapacity, or
- is life-threatening or results in death, If a serious event occurs the research project will be set on hold.

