##### **3.1. Risk categorization**

The study's risk category is A. This decision is based on the fact that the planned measures for sampling biological material or collecting personal data entail only minimal risks and burdens.

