### **4.3 Risk-Benefit Assessment**

The study participants will benefit from a free screening for cervical cancer with HPV test. HPV- positive women will undergo, Pap smear, ECC, VIA/VILI and biopsy. Those with positive VIA will immediately be treated by thermal ablation or LEEP (if not eligible to thermal ablation). All cancer and pre-cancer detected will have free of charge management.

Voluntary women will be addressed to the HIV department for screening and free treatment. Patients with fistulas will be transferred to the University Teaching Hospital of Yaoundé and will be freely treated (collaboration between Pr [name] and the Swiss NGO “fistula- group” lead by [name], Geneva).

We expect that our data will determine how a CC-screening program might be established in a sustainable prevention strategy. The data will also determine the level of support, which will be needed to maintain high-quality CC prevention services in equipment and provider skills. In addition, the developed AVC tool will assist medical staff in their assessment of VIA and reduce the subjectivity of the process.

One possible risk is the unauthorized data access or unwanted identification of project participants. Another risk though very low is the occurrence of side effects following biopsy and thermal coagulation (light pelvic pain, light vaginal bleeding or watery discharge).

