#### **5.1.2 Secondary objectives:**

- To create a database of cervical images for continuous clinical education
- To assess the impact of HPV-positive screening on the level the women's quality of life among women in Cameroon
- To examine the impact of the screening on sexual and reproductive health among women with HPV.
- To assess the impact of HPV-positive screening on the level of anxiety among women.
- To better understand the accessibility of HPV-self sampling and potential barriers to screening
- To inform women and their families about gynecological pathologies, including cervical cancer, sexually transmitted diseases (including HIV) and vaginal fistula
- To assess women acceptability of self-HPV, thermal ablation and screening process
- To study the HPV infection positivity and clearance, as well as prevalence of cervical cancer and pre-cancer
- To assess thermal ablation efficacy for the treatment of precancerous lesions
- To offer the possibility to perform HIV test in HIV center in Dschang
- To expand coverage and improve access to cervical cancer screening programs with participation of community health workers.
- To assess the impact of thermal ablation on fertility and obstetrical outcomes
- To develop a detection algorithm using cervical images that can identify cervical precancerous lesion
- To develop an Automated VIA Classifier (AVC) that can help identify cervical precancerous lesions based on a 2-minute video of the cervix during VIA and machine learning
- To assess women's, the community's and healthcare providers' acceptability of the AVC test
- To assess the AVC test performance.

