### 5.2.2 Secondary endpoint/outcomes

- Provide teaching material for professional training on cervical cancer prevention through VIA/VILI (cervical images database)
- Sexual dysfunction score, score of anxiety and method of contraception after screening procedures
- Willingness to participate in the 3T screening program;
- Prevalence of HPV, cervical pre-cancer and cancer among Cameroonian women
- HPV clearance at 6 and 12 months follow up
- Prevalence of CIN2+ disease at the 12-month follow-up
- Acceptability of self-HPV test, thermal ablation and cervical cancer screening procedures
- Women's experiences and attitudes on cervical cancer screening
- Proportion of side effects and complications after thermal ablation or LEEP
- VIA test-positive rate (HPV-positive women);
- VIA test-positive rate after 1- year follow-up of VIA-negative tests
- Thermal ablation efficacy
- Increase awareness on gynecological pathologies, including cervical cancer, sexually transmitted diseases and HIV, vaginal fistula in the community of the study area
- Number of women screened with and without the participation of community health care workers.
- Specificity and sensitivity of the AVC test, using histology as the reference standard
- Acceptability of the AVC test

The demand for programs to control CC in low-resource settings is strong. Lessons that we have learned from our previous experience, combined with results of recent researches have put our group in an excellent position to identify innovative and cost-effective strategies for reducing CC morbidity and mortality in developing countries. The obtained data will determine the level of support, which will be needed to maintain high-quality CC prevention services in equipment and provider skills. We expect also that our data will also determine how a CC- screening program might be established in a sustainable prevention strategy.

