#### First visit

- Information about the study and written informed consent
- Information about cervical cancer, STDs (including HIV) and fistula will be given to women;
- Socio-demographic data, acceptability of the self-test and data on women's quality of life will be collected according to validated questionnaire;
- HPV tests will be carried out on self-collected vaginal (flocked swabs transported in a 0.9% sodium chloride) medium samples using the GeneXpert machine. The results will be available after one hour.
- HPV-negative women will be reassured and advised to do the next screening 5 years later.
- HPV-positive women will undergo the following sequence on the same day: VIA/VILI > Pap smear

- > Cervical Biopsy (VIA-guided biopsy for VIA-positive participants and random biopsy for VIA-negative participants) > Endocervical Curettage (ECC). These tests will be done by the following experienced physicians.
- Pictures of the cervix during VIA/VILI (native image, video during acetic acid and image after lugol's iodine) will be stored on a digital device.
- VIA/VILI will be interpreted on smartphone pictures according to the ABCD criteria (relaxed IARC criteria).
- All participants with a positive VIA/VILI will be treated with thermal ablation if eligible or Loop Electrosurgical Excision Procedure (LEEP for participants ineligible to thermal ablation).
- Specimens of Pap smear will be transported in BD SurePath™ vials (Becton Dickinson Company, Franklin Lakes New Jersey, USA) while those of biopsy, LEEP and ECC will be transported separately in formol (formaldehyde solution) vials.
- Cytological and histological analyzes will be conducted both in Yaoundé and in Geneva.

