### **8.5.3 Reporting of SAEs, Safety and Protective Measures**

#### *Reporting of SAEs*

All SAEs will be reported immediately and within a maximum of 24 hours to the Sponsor- Investigator of the study. The Sponsor-Investigator will re-evaluate the SAE and return the form to the site. SAEs resulting in death will be reported to the local Ethics Committee (via local Investigator) within 7 days.

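### The serious-event definition does not name treatment, so a serious event due to thermal ablation alone falls outside it, and the undefined SAE and SUSAR terms do not close the gap

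*Protocol*

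**What the plan says.** Protocol section 8.5.1 gives the only definition in the safety chapter. Its causality test covers "any unfavorable event for which a causal relationship to sampling of biological material or the collection of health related personal data cannot be ruled out". A seriousness criterion must be met as well: hospitalisation, lasting disability, danger to life or death. The same section attaches a consequence: "If a serious event occurs the research project will be set on hold". Section 8.5.2 requires SEs to be entered in the participant's file and on an SE report form. Its descriptive text deals with acetic acid, iodine and cell and tissue specimens.

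Treatment is nevertheless part of the protocol. Under First visit in section 6.1.2: "All participants with a positive VIA/VILI will be treated with thermal ablation if eligible or Loop Electrosurgical Excision Procedure". Section 5.1.2 lists the objective "To assess thermal ablation efficacy for the treatment of precancerous lesions", and section 5.2.2 lists the outcome "Proportion of side effects and complications after thermal ablation or LEEP". Section 4.3 acknowledges treatment risk: "Another risk though very low is the occurrence of side effects following biopsy and thermal coagulation".

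Section 8.5.3 then changes vocabulary: "All SAEs will be reported immediately and within a maximum of 24 hours to the Sponsor- Investigator of the study". It goes on to set deadlines for SUSARs and safety signals. Section 9.2 records SAEs, not SEs, in the paper case report form.

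**The concern.** The causality test in 8.5.1 fits a project that only takes specimens and collects data. This protocol also treats women, and thermal ablation removes no tissue for the laboratory. A woman admitted to hospital because of ablation alone would meet a seriousness criterion but fail the causality test, so her event would not be an SE.

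What is at stake is consistent handling. The SE report form and the project-hold sentence attach to SEs, while the 24-hour duty attaches to SAEs. If one term leaves out treatment and the other has no definition, two members of staff could both follow the text and deal differently with the same admission.

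**Working it through.** The point concerns wording. No figure in the plan depends on it, so the check sets the sections side by side and then looks at what can be said about scale.

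**1. Is treatment covered by the definition?** The causality limb has two branches, sampling and data collection. No other section extends it. The rationale for the risk category has the same two branches: it says that "the planned measures for sampling biological material or collecting personal data entail only minimal risks and burdens".

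**2. Which treatment events fall outside?** The test is whether a link to sampling can be ruled out, not whether sampling was the cause.
- *Thermal ablation on the day of biopsy and curettage.* For events such as bleeding, a link to the biopsy or curettage often cannot be excluded, so the event qualifies. An event due to ablation alone does not.
- *Thermal ablation at a later visit.* Under Visit to inform results in section 6.1.2, women with abnormal results may be treated by ablation or LEEP after the results are back. Biopsy and ablation are then separated in time, and a link to sampling is easier to exclude. This is the clearest case.
- *LEEP.* The First visit text lists LEEP with biopsy and curettage among the specimens sent in formaldehyde. A LEEP complication can therefore be read as related to sampling. The wording does not settle it.

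**3. Does the reporting section repair this?** The abbreviation list contains SE but neither SAE nor SUSAR. SUSAR is spelled out in a heading of 8.5.3 but not defined. Two readings are open:
- SAE means SE. Then an event due to ablation alone carries no 24-hour duty as an SAE.
- SAE is wider than SE. Then the event is reportable within 24 hours, but the SE form and the hold sentence do not apply to it.

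Neither reading gives complete and uniform handling.

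**4. Scale.** Inputs from section 9.1: 6000 women, 20% HPV-positive, 10% CIN2+ among these, VIA sensitivity 60%, specificity 50%, drop-out 20%.
- Check on the inputs, with half-width 1.96 × √(p(1−p)/n): for sensitivity, 1.96 × √(0.6 × 0.4/96) = 9.8%; for specificity, 1.96 × √(0.5 × 0.5/864) = 3.3%. Both match the protocol.
- HPV-positive: 6000 × 0.20 = 1200. CIN2+: 1200 × 0.10 = 120. Not CIN2+: 1080.
- VIA-positive, hence assigned to treatment: 0.60 × 120 + 0.50 × 1080 = 72 + 540 = 612, or 51% of 1200. With drop-out applied: 0.8 × 612 ≈ 490.
- CIN2+ but VIA-negative, hence treated only on recall: 120 − 72 = 48 at most, before drop-out.

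These are counts of women assigned to treatment, not of events outside the definition. The protocol gives no split between ablation and LEEP. The figure of about 250 ablation-treated women in section 6.1.2 is a group size for the fertility survey and is not stated to be the total ablated. The protocol also gives no serious-complication rate. The number of affected events therefore cannot be derived.

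**The case against.** The case on the other side is substantial and narrows the point.

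- **LEEP and same-day events.** LEEP produces a specimen, and the cannot-be-ruled-out test is generous when biopsy and curettage happen on the same day. This stands. A reader might infer that all 612 + 48 = 660 treatments lie outside the definition and, with an assumed serious-complication rate of 0.5% to 2%, that 3 to 13 events would be missed. The documents do not support that: many such events would still qualify as SEs, and the rate comes from no section of the protocol.
- **The complications outcome.** A reader might infer that the outcome in 5.2.2 would be under-counted. It names treatment directly and is not filtered through the SE definition, so this does not follow.
- **Other safety routes.** The SAE duty in 8.5.3 carries no sampling restriction, safety signals cover new risks and new aspects of known reactions, section 10.1 keeps records of adverse reactions, and section 11.3 provides for managing complications. It would be wrong to say that treatment harms go unreported. But the SAE route rests on an undefined term, the safety-signal route is not aimed at individual serious events, and none of these places a treatment event within the SE definition.
- **Declared project type.** The synopsis and section 6.1.1 class the study as sampling and data research, and section 3.1 places the management of dysplasia under outside recommendations. The definition matches that class. It does not match a protocol that also assigns the treatment and makes its efficacy and complications study questions.

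**Conclusion.** The point holds in a limited form. As written, a serious event attributable to thermal ablation alone is not an SE, most clearly when ablation follows at a recall visit, and SE documentation then does not apply. LEEP is ambiguous. The undefined SAE and SUSAR terms add an inconsistency and do not repair the definition.

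This rests on the literal text and on no assumed rate. The only supportable figure for scale is that about 612 of 1200 HPV-positive women are expected to be assigned to treatment before drop-out, if the section 9.1 assumptions hold. The number of events affected is unknown. The point does not touch the sensitivity and specificity analysis. It is a wording defect in the safety chapter that the sponsor should correct, because a small amendment removes it.

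**What to change.** - In 8.5.1, extend the causality phrase to any study procedure, naming biopsy, endocervical curettage, thermal ablation and LEEP, and keep data collection.
- Use one defined serious-event term throughout 8.5.1 to 8.5.3 and in 9.2. Where SUSAR is kept, define it.
- Leave the complications outcome in 5.2.2 covering all side effects and complications, serious or not. Applying the serious-event term there would narrow it.
- A wider definition also widens what triggers the hold sentence in 8.5.1. The sponsor must reconcile the two; no particular rule is proposed here.

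The cost is amendment wording, an updated SE form and slightly more reporting.

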### **8.5.2 Assessment and Documentation of SEs**

Application and interpretation of the VIA results will be conducted as recommended by the WHO. « Relaxed » VIA criteria will be used, meaning that any whitening of the cervix after acetic acid application will be considered as positive (to reduce false negative rate). Application of acetic acid on the cervix may cause a slight burning sensation, which disappears after a few minutes. The application of iodine does not cause any discomfort if not a change in color of the cervical surface, but the normal color returns a few minutes after the procedure. As for the cell and tissue specimens, minor pain and/or bleeding may be observed after sampling. But most often, these inconveniences are harmless and disappear within hours after the procedure. All the SEs will be documented in the participants' file and on the SE report form.

### **8.5.3 Reporting of SAEs, Safety and Protective Measures**

#### *Reporting of SAEs*

All SAEs will be reported immediately and within a maximum of 24 hours to the Sponsor- Investigator of the study. The Sponsor-Investigator will re-evaluate the SAE and return the form to the site. SAEs resulting in death will be reported to the local Ethics Committee (via local Investigator) within 7 days.

#### *Reporting of Suspected Unexpected Serious Adverse Reactions (SUSARs)*

A SUSAR will be reported to the local Ethics Committee (local event via local Investigator) within 7 days, if the event is fatal, or within 15 days (all other events).

#### *Reporting of Safety Signals*

All suspected new risks and relevant new aspects of known adverse reactions that require safety-related measures, i.e. so called safety signals, must be reported to the Sponsor- Investigator within 24 hours. The Sponsor-Investigator must report the safety signals within 7 days to the local Ethics Committee (local event via local Investigator).

#### *Reporting and Handling of Pregnancies*

Our study will not include pregnant participants. Any pregnancy occurring during the study will be reported to the Sponsor-Investigator within 24 hours. Those women found with CIN2+ will be followed throughout the pregnancy and six weeks after birth evaluation and the treatment of the CIN2+ will be offered to them. Those normal cytology and histology results will be seen at the follow visit six weeks after delivery for HPV-test, Pap smear and ECC. All participants exiting the study due to a SAE will be monitored until the complete resolution of symptoms and signs. Efforts will be made in order to minimize any loss to follow-up, through supervision by the most experienced local physician.

## **9. STATISTICAL METHODOLOGY**

### **9.1 Determination of Sample Size**

We plan to include 6000 women in the study. Assuming a prevalence of HPV infection of 20%, 1200 participants will be HPV+. Among the awaited 1200 HPV+ women, 120 will have CIN2+ lesions (assuming a prevalence of CIN2+ of 10% among HPV+ women). Assuming a 20% drop-out rate, 96 cases of CIN2+ will be analyzed to determine the sensitivity of VIA (expected around 60%) with a precision of +/- 9.8%.

Among the awaited 1200 HPV+ women, 1080 will not have CIN2+ lesions. With a drop-out rate of 20%, 864 cases of non-CIN2+ will be analyzed to determine the specificity of VIA (expected around 50%) with a precision of +/- 3.3%.

### **9.2 Data processing**

Study data will be recorded with paper Case Report Forms (p-CRF). The p-CRF will be coded with the patient's number of inclusion in the study. Only the study's investigators will be authorized to enter data in the p-CRF. Data from the p-CRFs will then be transferred into an electronic database for analysis.

Some data will be collected directly in the p-CRF because in the study areas there are no complete medical files. This will include socio-demographic and medical parameters, visit dates, randomization number, SAEs and test results. Nevertheless, some tests results (HPV- test results, cytology and histology reports) will be available in laboratories as source data.

Data entry from the p-CRF into the electronic database using Secutrial® software will be done during the study. At the end of the study, all data will be double checked in order to guarantee accuracy. Any discordance will be clarified by calling the participant. All data in the p-CRF and in the electronic database will only refer to patients by their anonymity number.

The coded data used for the development of the AVC test will be stored on a Secure File Server (NAS) accessible only to the authorized personnel with a personalized authentication system.

### **9.3 Planned analysis**

#### **9.3.1 Datasets to be analyzed**

Data from all complete electronic CRFs will be analysed. We will carry out our analyses using the software package STATA® 14 (Stata, College Station, TX, USA). All p-values of <0.05 will be considered statistically significant. Sensitivity, specificity, positive and negative predictive values of VIA/VILI will be calculated using histology as gold standard. The aforementioned trial statisticians will perform these analyses.

Qualitative interviews (e.g. focus groups discussions or individual interviews) will be recorded, and

transcribed. The transcripts will be analyzed using the software ATLAS.ti.CAQDAS or manually applying the qualitative content analysis according to Mayring. [11]

### **9.3.2 Handling of missing data**

Missing data will be reported as such. Drop-outs will be replaced.

### **9.3.3 Deviations from the original statistical plan**

Any deviations from the planned analyses will be justified and reported in the final manuscript.

## **10. DATA AND QUALITY MANAGEMENT**

### **10.1 Data handling and record keeping / archiving**

Each participant's signed informed consent form and personal information (including the socio-demographic questionnaires and the post-treatment assessment) will be classified by participant anonymity number and stored in a closet to which only the designed medical personnel will have access through the use of key. Prior to the beginning of the study (enrollment of participants) the principal investigator will organize a training session for all the study personnel. Copies of all the study documents will be kept study master file secured at the study in a safe while originals will be kept by the sponsor-principal investigator. Access to that safe will be limited to the site coordinating investigator and to designated co-investigator. These documents include (source/data documents): ethical and administrative clearances, advertising messages, anonymity list, participants information sheets with signed informed consent, pCRFs, results of HPV test, cytological and histological analyses, electronic drives and smartphones containing pictures of the cervix, records of adverse reactions, curriculum vitae of study personnel and reports of monitoring visits and audits).

Relevant clinical information along with the videos taken during VIA will be transferred to EPFL in order to develop an AVC tool. Only coded data is transferred.

### **10.2 Data transfer**

Exports of all or any kind of partial data will be systematically password-protected before being transferred and only coded data will be used.

Data from the p-CRF is entered into the electronic database using Secutrial® software in Cameroon and does not necessitates any transfer to be accessible from HUG.

The native/VIA/VILI photos and VIA videos are taken with a password-protected smartphone that is only dedicated for that purpose. A mobile application is being specifically developed to collect the images and to securely transfer them to a secure file server (NAS) at EPFL via an API hosted on a private EPFL server, using HTTPS.

